#### Adaptive PK study procedure

After screening, subject eligibility will be reconfirmed on the Day 1 of V2, before the first dose of the study medication. The blood sampling for PK studies will be done at V2 (Day 1) and V3 (Day 4). The amount of blood withdrawn will depend on the age and weight of the patient and mostly follow the 5-sample schedule for PK studies. Further, the blood samples will also be used for safety laboratory assessments (haematology and clinical chemistry tests) (Table 2).

The patients will be enrolled in specific age groups (birth to 1 year, 1 to 2 years, 2 to 6 years, 6 to 12 years, and 12 up to and including 17 years) (Fig. 1). The PK and safety data of the patients (at least 3 patients) in each age group will be analysed to establish the paediatric-equivalent dose (PED) that will be used in the DBPC phase of the study. After completion of the PK assessments and analysis per age group (minimum 3 patients), a Data and Safety Monitoring Board (DSMB) will review the safety and PK data. It will issue an official recommendation on the safety of the study subjects and the proposed dose in the specific age group. This may lead to a change in sonlicromanol dose for one or more age groups. This DSMB recommendation letter will be submitted to the Medical Research Ethics Committee (MREC) for approval. After receiving MREC’s approval on the DSMB recommendation, the patients in the specific age group will be enrolled in the DBPC phase of the study. The adaptive PK study with the anticipated PED will be initially conducted in the elder children: older age groups will be studied before younger age groups.

#### Double-blind, placebo-controlled phase

All the patients completing the first phase of the study (the Adaptive PK study) will be offered participation in the DBPC phase. When a minimum of three subjects in each age cohort has completed the Adaptive PK phase, new participants from that age group may be enrolled, directly in the DBPC phase without having to participate in the Adaptive PK study.

In this second phase, subjects will be randomised (by age group) in a 1:1 ratio (using block size of 4) over two arms using *Lifesphere* EDC and *Lifesphere* Central Coding (vendor: *ArisGlobal*) [44] The allocation of randomization sequence is fully integrated into the *LifeSphere* EDC system and is blinded to the patient, caretaker and the researcher. The randomization number will be automatically generated by *Lifeshpere* EDC [44] and will be used for assigning the subjects to the treatment groups. Arm 1 will receive oral sonlicromanol (PED) twice daily for 26 weeks (6 months), while Arm 2 will receive a matching placebo twice daily for 26 weeks (6 months). The patients and/or parents/caregivers will be required to maintain the patients’ daily diaries. The patients’ eligibility will be reconfirmed on Day 1 of the treatment period (V4) before randomisation. Further, the patients will be assessed for all the clinical and safety outcome measures at each visit during the treatment phase. Table 2 describes the detailed study procedures. A final follow-up visit (V8) will be scheduled two weeks after the intake of the last dose of the treatment period. Study medication will be collected at each visit, after which, new study medication kits will be provided. All the remaining study medications will be collected during the final visit.

#### Withdrawal procedure

Premature discontinuation from the study will occur whenever the participant does not finish the scheduled 26 weeks treatment period and the follow-up assessment. The participants will be allowed to prematurely terminate the study at any time or be excluded from the study at the investigator’s decision if continuous administration of the study drug is thought not to be in the participant’s best interests. Also, the participant will be discontinued by the investigator or the sponsor (designee) if enrolment into the study is found inappropriate, the study plan is violated, and/or for any other safety reasons. Mandatory withdrawal criteria will be applicable when QTc exceeds the 95th percentile for the age- and sex-dependent QTc interval or if female participants become pregnant. Withdrawal of the assent/(co-)consent by subject/parents/caregiver or loss to follow-up will also lead to premature termination. Failure or refusal of blood sampling for the PK assessment at Day 4 (V3) of the PK study will also be treated as a withdrawal of consent and result in termination of the participant.

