#### Exclusion criteria

The exclusion criteria of the study are described below:Participants who have undergone gastrointestinal surgery with removal of stomach or duodenum/jejunum segments that interfere with absorption (feeding via gastrostomy tube will be permitted).Prior treatment with an investigational drug within 3 months or 5 times the half-lives of the investigational drug (whichever is longer) before the first dose of the study drug.Clinically significant cardiovascular disease or risk factors for arrhythmia based on judgement by the investigator likeAbnormal ECG (including QTcF exceeding the 95th percentile for the age- and sex-dependent QTc interval) and/orAbnormality detected in 2D ECHO.Systolic Blood Pressure (SBP) above the 95th percentile for the sex, age group, and height percentile at screening or baseline on a single measurement.Any history of acute/chronic heart failure.History of unexplained syncope.Family history or medical history of congenital long and short QT syndrome or sudden death.Hyper- or hypo-kalaemia; hyper- and hypomagnesaemia; hyper or hypocalcaemia.Clinically significant abnormal laboratory findings such asAspartate aminotransferase (ASAT), alanine aminotransferase (ALAT), or bilirubin >3 times the upper limit of normal (ULN) (If ASAT or ALAT >3 times but <3.5 times the ULN, re-assessment will be performed at the investigator’s decision).Estimated glomerular filtration rate (eGFR) (based on the formula: 40.9*((1.8/Cystatine C) ^0.93^) below age-appropriate limits: < 2 months: < 25 ml/min/1.73 m^2^, 2 months to 1 year: < 35 ml/min/1.73 m^2^, > 1 year: < 60 ml/min/1.73 m^2^.The investigator will judge other clinically significant parameters at screening or baseline.History of hypersensitivity to any of the components of the investigational drug.Medical history of drug abuse (use of narcotic agents such as cannabinoids, amphetamines, cocaine, opiates, or misuse of prescription drugs such as benzodiazepines, opiates).The use of any drug and/or supplements within 4 weeks or 5 times the half-life (whichever will be longer) before the first dose of the study drug, unless stable for at least one month before first dosing and remaining stable throughout the study. These includes(Multi)vitamins, coenzyme Q10, vitamin E, riboflavin, and antioxidant supplements (including, but not limited to idebenone/EPI-743, mitoQ).Any medication that influences the mitochondrial functioning negatively (including but not limited to valproic acid, glitazones, statins, anti-virals, amiodarone, and non-steroidal anti-inflammatory drugs),Any strong cytochrome P450 (CYP)3A4 inhibitors (all conazoles-anti-fungal, HIV antivirals, grapefruit) or CYP3A4 inducers (including HIV antivirals, carbamazepine, phenobarbital, phenytoin, rifampicine, St. John’s wort, pioglitazone, troglitazone).Any drug known to disturb cardiac repolarisation, unless the QTc interval at screening is normal during stable treatment for a period of two weeks, or 5 half-lives of the drug and its major metabolite(s), whichever is shorter (all antipsychotics, certain anti-depressants such as nortriptyline or amitriptyline, fluoxetine, anti-emetics like domperidone, granisetron, ondansetron).Any drug metabolised by CYP3A4 with a narrow therapeutic index.

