^b^Assessments are also to be performed in case of premature discontinuation

^c^Demographics, Medical history on V4 only for patients not participating in the Adaptive PK study

^d^Including haematology and clinical chemistry parameters. Metabolomics and biomarkers in plasma and urine (overnight sampled portion or first-morning urine portion to be collected before early morning food/drinks intake) at V4 and V7. For patients with heteroplasmic mitochondrial DNA mutations: mtDNA heteroplasmy assessment in urine at V4 and V7

^e^Only for patients with heteroplasmic mitochondrial DNA mutations: mtDNA heteroplasmy assessment in urine at V4

^f^In females with childbearing potential only, as defined in section 3.2.9. Pregnancy blood test at screening, urine (dipstick) tests at monthly intervals, and at the Follow-up visit. Females of childbearing potential will be provided with urine (dipstick) pregnancy tests and will be instructed to perform the pregnancy tests at home, at monthly intervals throughout the double-blind study treatment period. The female subjects (or parent/caregiver) will be contacted by the study staff each month to report the results of the pregnancy tests

^g^For subjects <3 years: height, weight, skull circumference, and weight-for-height will be assessed. For subjects>3 years, weight, height, and BMI will be assessed

^h^Bodyweight only

^i^Including supine blood pressure and heart rate. Vital signs are to be recorded as close as possible to each PK assessment at V2, 3, and 7

^j^As close as possible before each sampling timepoint of the PK assessment

^k^ECGs will be recorded at Screening, Day 1 (V2) before first dosing on day 1; on Day 4 (V3) and Visit 7 just before the PK sample assessments; at day 1 (V4), at month 1 (V5), month 3 (V6), at month 6 (V7, just before the PK sample assessments) and Follow-up (V8)

^l^Not to be done if documented (favourable) result dated less than 6 months prior to screening is available

^m^Before trial, medication intake

^n^This is a training session to reduce the learning effect. By conducting the learning session at the screening visit, the testing burden at V4 is reduced

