### Statistical analysis

All statistical analyses will be performed using the SAS® System (SAS Institute Inc., Cary, NC, USA). Continuous data will be presented using descriptive statistics where the parameters will be reported such as n (number of observations), mean, SD, minimum (Min), median and maximum (Max). Geometric means will be used for PK variables (AUC and C_max_). Absolute and relative frequencies will be utilised to analyse categorical variables. Unless otherwise specified, all tests will be two-sided at the 5% level, and all the confidence intervals will be two-sided at the 95% level. Given the number of assessments conducted in this trial, the SAP will include appropriate corrections for multiple testing using a hierarchical procedure and/or alpha correction.

Four different analyses sets will be applied for performing the statistical analysis, namely: all-randomised, all-treated, safety, and per-protocol (PP) sets. The populations used in the efficacy analyses of the DBPC phase will be the all-randomised and PP populations. The all-randomised population will consist of all patients randomised for the double-blinded treatment, regardless of whether they received the study medication or not, consistent with the Intention-to-Treat (ITT) principle. The primary efficacy endpoint (change in GMFM-88 score) at weeks 6, 13, 27, and 29 will be performed using the all-randomized and PP population. The PP population will consist of all patients in the all-treated set who will not violate the protocol in a way that could affect the primary outcome measure. The population for assessing the safety will consist of all patients in the safety set. This population will include all randomised patients receiving the study medication and for whom at least one safety assessment (after first drug intake) is available (patients are assigned the treatment actually received). Descriptive statistics will be used to analyse the safety data. The demographics, subject disease characteristics, and baseline data (including medical history) will be presented descriptively for the PK study (V1 or V2) and DBPC study (V4).

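### The withdrawal rule takes any child who violates the study plan out of the trial, while the analysis section needs violators to stay under observation

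*Protocol article*

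**What the plan says.** Four parts of the protocol article bear on this.

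- **Withdrawal procedure.** A participant will be "discontinued by the investigator or the sponsor (designee) if enrolment into the study is found inappropriate, the study plan is violated", or for other reasons of safety. The section defines its subject broadly: "Premature discontinuation from the study will occur whenever the participant does not finish the scheduled 26 weeks treatment period and the follow-up assessment". The event described is therefore leaving the study, including follow-up.
- **Statistical analysis.** The all-randomised set holds every randomised patient, "consistent with the Intention-to-Treat (ITT) principle", and the primary endpoint is analysed at weeks 6, 13, 27 and 29. The per-protocol set consists of "all patients in the all-treated set who will not violate the protocol in a way that could affect the primary outcome measure".
- **Table 2, note b (attached to V7).** "Assessments are also to be performed in case of premature discontinuation". V7 includes GMFM-88. Nothing in the article keeps a discontinued child on the remaining visits.
- **Exclusion criteria.** Use of listed drugs and supplements excludes a child "unless stable for at least one month before first dosing and remaining stable throughout the study", so an eligibility criterion reaches into the treatment period.

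**The concern.** The two sections treat a protocol violation differently. The analysis section grades violations: all violators remain in the all-randomised set, and only those whose violation bears on the primary outcome leave the per-protocol set. That grading is useful only if violators continue to be observed. The withdrawal section does not grade them and, taken at its word, ends participation. A dose taken outside the allowed interval or a visit outside its window would be enough.

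Two things are at stake. The first is precision: in a trial of 24 children each removal is 1/12, or 8.3%, of an arm. The second is selection after randomisation. If violations are more frequent in children who are getting worse, for example because their treatment is changed, the children who remain on schedule differ from those who were randomised. A late finding that enrolment was inappropriate works in the same way, since it removes a child who already belongs to the intention-to-treat set.

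**Working it through.** **1. Which scheduled GMFM-88 values are lost.** Post-baseline assessments are V5 (week 6), V6 (week 13), V7 (week 27) and V8 (week 29). Under the literal rule plus note b:

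- removal before week 6 replaces four scheduled values by one early V7 assessment;
- removal between weeks 6 and 13 replaces three;
- removal between weeks 13 and 27 replaces two.

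A child removed before week 13 is unobserved for at least 27 − 13 = 14 weeks before the six-month time point.

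**2. The plan's own sample-size figure.** Inputs from Power and sample size calculation and Statistical analysis: difference 4%, SD between 2 and 4.5%, power 80%, 12 per group, two-sided 5%. No single SD is given, so there is no unique figure to reproduce. The normal formula n = 2(1.96 + 0.84)² SD²/4² per arm gives 4, 11 and 20 at SD 2, 3.25 (mid-range) and 4.5. The two-sample t calculation gives 6, 12 and 21. Twelve per arm thus fits the middle of the range and reaches 80% up to an SD of about 3.34 (t). The 24 children planned equal 2 × 12, so the stated number leaves no room for loss.

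**3. Effect of removals on power.** Assumptions: removed children give no usable week-27 value, losses are equal in the two arms, and the analysis is a two-sample t-test with noncentrality (4/SD)·√(n/2) and 2n − 2 degrees of freedom. The document states no removal rate, so 0 to 4 per arm are shown.

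| Children per arm with a week-27 value | SD 2 | SD 3.25 | SD 4.5 |
|---|---|---|---|
| 12 | 99.7% | 82.1% | 54.9% |
| 11 | 99.4% | 78.4% | 51.0% |
| 10 | 98.8% | 74.0% | 46.9% |
| 9 | 97.8% | 68.9% | 42.6% |
| 8 | 96.0% | 63.0% | 38.1% |

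**4. Bias.** If k of 12 children in an arm drop out of the week-27 mean, and their mean change would have differed by D from that of the children who remain, the observed arm mean is off by (k/12)·D. The document gives neither k nor D for either arm, so the formula shows only what the bias depends on.

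**5. Co-medication.** The Withdrawal procedure does not mention it. The link takes two steps: the exclusion criterion asks for stability during the study, and a breach of it could count as a plan violation or as inappropriate enrolment. This is clearest for a change to an existing listed treatment. It is weaker for a newly started drug, because the criterion opens with use before the first dose.

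**The case against.** The strongest reply is that the sentence was never meant to cover every violation. It ends by adding 'other' safety reasons, which can be read as marking the earlier grounds as safety grounds too. The next sentence sets out mandatory withdrawal criteria and names only QTc prolongation and pregnancy, a label with little purpose if every violation already forced removal. Eligibility is checked at V1, V2 and V4 only, and the child's "eligibility will be reconfirmed on Day 1 of the treatment period (V4) before randomisation"; after that, concomitant medication is simply recorded. The article also condenses a longer protocol, where deviation rules may be set out. These cues make a narrower intention plausible, but the wording remains mandatory and unqualified, and a site following it would remove the child.

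Three stronger readings are tempting and are not supported.

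- A reader might infer that unstable co-medication is a stated ground for removal. It is an inference from the exclusion criteria.
- A reader might infer that children are removed because of their outcome. The document does not say so, and the rule equally covers violations unrelated to outcome.
- A reader might put a number on the bias. For example, if 3 of 12 placebo children worsened by 5 points and were removed while the other 9 had a mean change of 0, the placebo mean would be off by 3 × 5/12 = 1.25 points, or 31% of the 4-point target. This assumes the rate, places every removal in one arm, and ignores that note b has GMFM-88 assessed at discontinuation, so the worsening could be recorded. Medication changed because of an adverse event on active drug would be caught too, so even the direction is open.

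How an early V7 score enters the analysis is commonly left to the statistical analysis plan, which is not shown. That point stands, but no analysis can recover scheduled visits that did not take place.

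**Conclusion.** The point holds as an unreconciled conflict. Read as written, the withdrawal rule ends participation for any violation or late eligibility finding, while the analysis section relies on following all randomised children and uses the per-protocol set for outcome-relevant violations. The consequence is loss of GMFM-88 data after the violation, softened but not removed by one early V7 assessment.

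On the assumptions above, losing two children per arm at an SD of 3.25 costs about 8 percentage points of power (82.1% to 74.0%), and losing three costs about 13 (82.1% to 68.9%). These figures overstate the loss if the early V7 value is used. Bias is possible if violations relate to worsening, but its size and direction cannot be set from the document.

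**What to change.** Reconcile the Withdrawal procedure, the Exclusion criteria and the Statistical analysis section, so that they agree on whether a protocol violation or a late eligibility finding ends study participation or only affects per-protocol membership. In doing so:

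- separate the decision on study treatment, which stays a clinical matter and on which no rule is proposed here, from participation in study assessments;
- record violations, including changes in listed co-medication after randomisation, as dated deviations;
- continue the scheduled assessments through V7 and V8 for these children where consent stands, so that the all-randomised analysis can use them.

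The stability clause in the exclusion criteria should be part of the reconciliation and not simply shortened, because its list includes QT-affecting and CYP3A4-related drugs and may serve safety.

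The cost is protocol wording and continued visits for a few children; concomitant medication is already recorded continuously. The statistical downside is some dilution of the effect in the all-randomised analysis, which the planned per-protocol analysis sits beside.

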### Study medication

The medicinal product under investigation is sonlicromanol, administered as an oral liquid. It will be manufactured and provided under the responsibility of the sponsor. Sonlicromanol, as well as the placebo, will be provided as a powder for oral solution. To maintain the blinding of the study, the placebo formulation will be matched to the active study medication in size, colour, shape, and taste. The investigational medicinal product and its matching placebo will be packaged in the same way, in glass bottles according to a randomisation list.

#### Route of administration and Dosage

Study medications (sonlicromanol and placebo) will be made available as a powder that must be dissolved in water. An oral syringe will be used to administer the solution in the correct volume. Patients with a nasogastric/ percutaneous endoscopic gastrostomy tube will be dosed through the stoma. The first daily dose should be taken in the morning, followed by the second after 12 h. A minimum 6-h allowable intake window will be provided, i.e., two doses must not be taken within 6 h of one another and not more than 18 h apart.

Sonlicromanol will be given in the anticipated PED for four days (Adaptive PK study), followed by sonlicromanol or placebo in the confirmed PED twice daily for 26 weeks (DBPC phase). According to Physiologically Based Pharmacokinetics (PBPK) model and the plasma concentration results from the PK phase, the anticipated PED will be administered in fixed doses, comparable in exposure to adults with PMDs treated at 100 mg, twice daily (Table 3).

**Table 3 Tab3:** Anticipated Paediatric-equivalent dose comparable to adults with mitochondrial disease treated at 100 mg twice daily

Population	Dose (mg) per administration (BID)
Neonates (0–28 days)	2
Infants (1–2.5 months)	4
Infants (2.5–12 months)	12
Toddlers (1–2 years)	23
Young Children (2–6 years)	33
Middle-Aged Children (6–12 Years)	55
Adolescents (12–17 years)	80

### Power and sample size calculation

There is limited information on GMFM-88 scores in the target population [45–48]. Based on the available information, the sample calculations were conducted assuming the standard deviation (SD) range between 2 and 4.5% and an effect size of 4% or 5%. A sample size of 12 (in each group) was calculated to achieve a power of 80%. This could detect a mean change from a baseline difference of 4% between the groups for the total GMFM-88 score.

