### Study participants

The study will be conducted in children (from birth up to and including 17 years) suffering from motor symptoms due to genetically confirmed PMD for which the gene defect is identified to decrease one or more OXPHOS system enzymes. Twenty-four (24) patients are planned to be randomised in the study.

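### The stated 80% power for a 4% GMFM-88 difference with 12 per group names no SD, and it holds over only part of the article's assumed SD range

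*Protocol article*

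**What the plan says.** The article's section on power and sample size opens with a caution about its inputs: "There is limited information on GMFM-88 scores in the target population". It describes calculations run "assuming the standard deviation (SD) range between 2 and 4.5% and an effect size of 4% or 5" per cent. One result follows: "A sample size of 12 (in each group) was calculated to achieve a power of 80" per cent. The next sentence attaches a difference to it: "This could detect a mean change from a baseline difference of 4% between the groups for the total GMFM-88 score".

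Three other places supply the rest. The study participants section gives the total: "Twenty-four (24) patients are planned to be randomised in the study". The section on the double-blind phase gives the allocation: "subjects will be randomised (by age group) in a 1:1 ratio (using block size of 4"). The statistical analysis section sets the general test rule: "Unless otherwise specified, all tests will be two-sided at the 5% level".

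The power section does not say which SD in the range goes with 12 per group, 80% and 4%. It also does not say whether the SD is that of the change score or of a score at one visit, or which test was used.

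**The concern.** An SD range whose top is more than twice its bottom cannot give one power figure for a fixed sample size and a fixed difference. The article prints the range and then one unqualified 80%, so a reader will naturally take the 80% to apply across the range. If it does not, the primary comparison could have much lower power than stated under values that the sponsor itself treated as plausible.

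The section admits that prior data are sparse, and the article's discussion stresses how heterogeneous these diseases are, so the upper end of the range cannot be set aside. What is at stake is how the result is read. A non-significant difference means one thing from a trial with 80% power for 4% and another from a trial with 55%.

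**Working it through.** **Inputs.** From the article: 12 per group, 1:1 allocation, two-sided 5%, difference 4% (alternative 5%), SD 2% to 4.5%. Assumed: the SD is that of the change from baseline, and the test is an unadjusted two-sample t-test.

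**Formula.** Power comes from the noncentral t distribution with 2 × 12 − 2 = 22 degrees of freedom and noncentrality

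λ = difference / (SD × √(2/12)) = difference / (SD × 0.408).

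**Step 1: reproduce the stated figure.** The midpoint of the range is (2 + 4.5)/2 = 3.25%. There λ = 4 / (3.25 × 0.408) = 3.01, the power is 82.1%, and the smallest sample giving 80% is exactly 12 per group. The t-test returns 12 per group for any SD from about 3.19% to 3.34%. The published combination is therefore attainable at a mid-range SD.

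**Step 2: find where it stops holding.** With 12 per group, 80% power requires a standardised difference of 1.197. For 4%, the largest SD is 4/1.197 = 3.34%. For 5%, it is 5/1.197 = 4.18%. The share of the assumed range above the first limit is (4.5 − 3.34)/(4.5 − 2) = 1.16/2.5, or about 46%.

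**Step 3: power across the range for a 4% difference.**

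| SD (%) | λ | Power |
|---|---|---|
| 2 | 4.90 | 99.7% |
| 3 | 3.27 | 87.7% |
| 3.25 | 3.01 | 82.1% |
| 3.34 | 2.93 | 80.1% |
| 4 | 2.45 | 64.9% |
| 4.5 | 2.18 | 54.9% |

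**Step 4: the upper end.** At SD 4.5%, a 5% difference gives λ = 5 / (4.5 × 0.408) = 2.72 and power 73.9%, so the larger effect does not restore 80% either. The difference detectable with 80% power there is 1.197 × 4.5 = 5.4%. For scale, 80% power for 4% at that SD would take 21 per group.

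**Step 5: sensitivity to method.** The normal approximation moves the SD limit for 4% to 3.50%, which leaves (4.5 − 3.50)/2.5 = 40% of the range below 80%, and it gives 58.6% at SD 4.5%. A one-sided 5% t-test gives 67.9% at SD 4.5%. Of the variants tried at that SD, only a one-sided test combined with a 5% effect exceeds 80% (83.9% by the t-test). That matches neither the two-sided rule nor the 4% attached to the claim.

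**The case against.** The strongest reply is that the section never says the 80% covers the whole range. It speaks of several calculations over a range of SDs and two effect sizes and then reports one outcome, which can be read as one row of a scenario table. The row exists, as Step 1 shows, and the full table may sit in the complete protocol, which is not shown. This stands in part: it rules out calling the figure a miscalculation. It does not rescue the wording. The article chose to print the range and an unconditional power side by side, and nothing tells the reader which row was taken.

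A second reply is that the SD is not labelled. If 4.5% were the SD at a single visit and the analysis adjusted for baseline, power at 4.5% would be about 67% with a baseline correlation of 0.5 and about 83% with 0.7. These correlations are illustrative, as the article gives none. This reply also stands as a caveat. The SD of change is the likelier reading because the detectable difference is stated in terms of change, but it remains an assumption.

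A reader might also infer that, because 24 is exactly 2 × 12, the calculation supposes that no child is lost. The document does not support pressing that. The article states no dropout policy and may leave it to the full protocol. The efficacy analysis includes all randomised patients, and footnote b of Table 2 schedules the V7 assessments at premature discontinuation, so a child who stops early is not necessarily without data.

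**Conclusion.** The point holds as a power claim that is not delivered over part of the article's own SD range. The 80% is supported for SDs up to about 3.3% and unsupported over roughly the top 46% of the range (40% by the normal approximation), with the lowest value, about 55%, at SD 4.5%. These figures rest on reading the SD as that of the change score and on an unadjusted two-sided 5% t-test.

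Two stronger conclusions are tempting. One is that the sample size calculation is arithmetically wrong. It is not, because it reproduces at the mid-range SD. The other is that the trial must recruit 21 per group. That would follow only if the true SD were known to lie at 4.5%, and the article gives no reason to prefer that value; at the lower end of the range power exceeds 99%.

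The severity is moderate. It should be fixed because the figure concerns the primary endpoint and shapes how a null result is read. It does not put the design in question.

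**What to change.** Keep 24 children and replace the unconditional statement with one that carries its condition, for example:

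> With 12 evaluable children per group, a two-sided 5% two-sample t-test has 80% power for a 4% between-group difference in GMFM-88 change if the SD of change is at most about 3.3%. Over the assumed SD range of 2% to 4.5%, power for 4% runs from more than 99% to 55%. At SD 4.5% the difference detectable with 80% power is about 5.4%.

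If the sponsor's calculation used a different SD definition or a baseline-adjusted analysis, the text should say so, give the assumed correlation, and quote the figures that follow.

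The cost is wording only. No patients are added, and the design and analysis do not change. The published power simply becomes less favourable over part of the range.
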